### Blinding

This is a double-blind (patients and clinicians are blinded) and double-dummy study [30]. A two-stage blind design was used. The first stage was group A, group B, and group C; the second stage was randomization to the experimental group, control group 1, and control group 2 according to SAS software, without correspondence to group A, group B, and group C. Treatment assignments will not be revealed until the whole process is complete. If patients have severe AEs, clinicians will log on to the central platform to unblind the patients as an emergency and provide relevant treatment. Once the blinding is broken, the patient with this number will be withdrawn from the trial and the clinicians will record the reasons in the case report form (CRF). To achieve blinding, all three groups will use the same kind of packaging to encase the drug or placebo. Size, color, shape, taste, smell, and packaging of the placebo are made identical to that of the corresponding medicine by adding artificial pigment.

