#### Exit criteria

Patients will leave the trial when one of the following criteria is met: (i) incorrectly included; (ii) are poorly compliant or pregnant; (iii) no medication or any follow-up records; (iv) occurrence of allergic reactions or serious adverse events (AE); (v) participants have other complications or special physiological changes during the trial; (vi) patients have been treated with other medicines during the trial; and (vii) not alleviated or the symptoms are aggravated. Participants may withdraw from the study at any time for any reason.

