## Follow-up

All included patients will be re-evaluated after seven days of treatment follow-ups as an outpatient to assess the efficacy and safety. The patients who were cured will receive the second follow-up after 28 days to assess the recurrence rate. Patients whose symptoms worsened will receive a supply of relevant medicine and a written withdrawal schedule. Assessment of study endpoints and duration of follow-up is shown in Fig. 2.

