### Safety assessments

Safety measurements included laboratory indices and AEs. All patients will undergo the following laboratory examination before enrollment and at the end of the clinical trial. Changes in laboratory indices before and after the clinical trial will be compared to conducting a safety analysis. Laboratory indices are: (i) routine blood and urine testing; (ii) liver function (AST, ALT, TBIL, DBIL, γ-GT, ALP) and kidney function (Scr, BUN); and (iii) ECG. The occurrence of any AEs in trial participants, such as subjective discomfort of patients and abnormal laboratory results, will be recorded in the CRF during the whole trial process. We will withdraw patients who have severe AEs, as it will be unsafe for them to continue the trial. Meanwhile, we will give them relevant medical care and follow them up until the reaction has terminated.

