### Data analysis

Data analysis will be performed by professional statisticians using SPSS 22.0. Three datasets will be conducted: intention-to-treat; per-protocol set; and safety dataset. The intention-to-treat refers to the patients who have been randomized; an intentional analysis will be conducted for curative effect. The per-protocol set refers to all cases that do not violate the protocol and complete the trial; per-protocol set analysis will be conducted for curative effect. The safety dataset refers to the randomized cases that have taken a tested drug at least once with safety evaluation data after treatment. We use mean ± standard deviation (SD) for continuous variables and percentages for categorical variables. In measured indices, the independent t-test will be used for hypothesis testing of the normal variables, while the Wilcoxon rank sum test will be used for hypothesis testing of the skewed variables. The χ^2^ test will be used for hypothesis testing of the counted indices. The statistical analyses will use the two-sided hypothesis test. *P* ≤ 0.05 will be set as the significant level.

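### Adverse-event exits and code breaks remove the patient from the trial rather than only from study drug, so planned day-7 outcomes may be lost in both non-inferiority comparisons

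*Protocol article*

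**What the plan says.** Three sections of the protocol article end participation after an adverse event or a code break.

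- **Exit criteria:** "Patients will leave the trial when one of the following criteria is met". Item (iv) of the list that follows covers allergic reactions and serious adverse events.
- **Blinding:** "If patients have severe AEs, clinicians will log on to the central platform to unblind the patients as an emergency". The consequence is then fixed: "Once the blinding is broken, the patient with this number will be withdrawn from the trial". The clinician records the reason in the case report form.
- **Safety assessments:** "We will withdraw patients who have severe AEs, as it will be unsafe for them to continue the trial". These patients receive medical care, and staff will "follow them up until the reaction has terminated".

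Two other sections bear on whether outcomes are still collected.

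- **Follow-up:** "All included patients will be re-evaluated after seven days of treatment follow-ups as an outpatient to assess the efficacy and safety".
- **Data analysis:** "The intention-to-treat refers to the patients who have been randomized", and this set is used for efficacy. The per-protocol set is limited to patients who complete the trial without violating the protocol.

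**The concern.** Stopping study drug and leaving the trial are different events. A safety problem justifies the first. It does not by itself justify giving up a symptom questionnaire, a urine test and a culture that are already scheduled. The article treats the two as one, and it adds a further exit route by making withdrawal the automatic result of breaking the code.

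The arms differ in active exposure (Interventions, Table 1). The experimental group takes Sanjin tablets without levofloxacin, control group 1 takes levofloxacin for seven days without Sanjin tablets, and control group 2 takes Sanjin tablets for seven days with levofloxacin for the first five. Adverse-event exits may therefore differ by arm, and so may missing primary outcomes. Both main aims are non-inferiority comparisons against control group 1. An intention-to-treat set of all randomised patients needs an outcome for each of them, and an outcome that was never collected can only be assumed.

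**Working it through.** **Reading the sections together**

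1. Exit criteria, Blinding and Safety assessments each refer to leaving, or being withdrawn from, the trial. None of them refers to stopping study drug alone.
2. After exit, the article names a recorded reason (Blinding) and care with follow-up of the reaction (Safety assessments). Neither is an efficacy assessment.
3. The Follow-up section places the visit after seven days of treatment. A patient taken out before then does not complete seven days of treatment, and the section does not say that withdrawn patients return.
4. The intention-to-treat definition keeps these patients in the denominator but does not supply their outcomes. The per-protocol set leaves them out because they did not complete the trial.

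So the rules as written allow day-7 efficacy data to be lost for these patients, and nothing in the article prevents it.

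**Illustrating the size**

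The article gives no figure on this point to reproduce and no adverse-event or code-break rate. The inputs are:

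- n = 252/3 = 84 per arm (Sample size; 1:1:1 allocation).
- p = 0.7714, the effective rate cited for Sanjin tablets (Sample size). Applying it to both compared arms is an assumption.
- Exits: 0 to 4 in one compared arm and none in the other (assumption), so e = exits/84 runs from 0 to 4.8%.
- r = true success rate among those who exit. The central assumption is p/2 = 0.386, with extremes of 0 and p.

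The shift in the difference (arm with exits minus arm without) is:

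- exits dropped from the denominator: (p − e·r)/(1 − e) − p
- exits counted as not effective: −e·r

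For 2 exits, e = 2/84 = 0.0238:

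- dropped: (0.7714 − 0.0238 × 0.386)/(1 − 0.0238) − 0.7714 = +0.009
- counted as not effective: −0.0238 × 0.386 = −0.009

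For 4 exits, e = 4/84 = 0.0476:

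- dropped: (0.7714 − 0.0476 × 0.386)/(1 − 0.0476) − 0.7714 = +0.019
- counted as not effective: −0.0476 × 0.386 = −0.018

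| Exits | r | Dropped (points) | Counted as not effective (points) |
|---|---|---|---|
| 2 | 38.6% | +0.9 | −0.9 |
| 4 | 38.6% | +1.9 | −1.8 |
| 4 | 0 | +3.9 | 0.0 |
| 4 | 77.14% | 0.0 | −3.7 |

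The signs hold as shown when the exits fall in the experimental group or control group 2, with the difference taken as that group minus control group 1. They reverse when the exits fall in control group 1. Non-inferiority therefore becomes easier to show if test-arm exits are dropped, or if control group 1 exits are counted as failures. With equal exits and the same r in both arms the shift is zero.

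**Scale**

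The standard error of a difference between two arms of 84 at 77.14% is √(2 × 0.7714 × 0.2286/84) = 0.065, or 6.5 points. The central shift for 4 exits is 1.9/6.5 ≈ 0.3 standard errors, and the largest is 3.9/6.5 = 0.6.

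**The case against.** **Loss of data is inferred, not stated.** The article never says that assessments stop after an exit. Follow-up refers to all included patients, and Safety assessments asks for laboratory tests, including routine urine, on all patients at the end of the trial. Withdrawal could have been meant as stopping treatment. That reading is possible, which is why the claim is only that outcomes may be lost. But the text says trial, not drug, in all three sections, and nothing reconciles the general visit statement with the exits.

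**The article condenses a fuller protocol.** Operational detail, such as form fields and unblinding logs, may sit there. This is fair for the detail. It does not change the stated rule, which is withdrawal from the trial.

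**The effect is small and assumed.** Known allergy to the test drug or quinolones is excluded, as is serious disease. Patients are under 50 and treatment lasts seven days, so events may be few. The illustrated shifts are well below one standard error, and an analysis plan could count exits as not effective. This stands, and it limits the weight of the point. Counting exits as failures removes the distortion only if they really are failures.

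**Keeping these patients has a cost.** The primary outcome is self-rated, and the article acknowledges its subjectivity, so a rating given after unblinding may be biased. This stands for the few patients concerned. Urine leukocytes and culture are less exposed, and an allergy exit under item (iv) needs no code break.

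**Other exits use the same wording.** Items (vi) and (vii), on other medicines and on lack of improvement, also take patients out of the trial and bear directly on efficacy. This is correct: the change proposed here does not recover those losses. It does not weaken the point about adverse events and code breaks.

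**Conclusion.** The concern holds. The article sets a rule that takes patients with allergic reactions, serious or severe adverse events, or a broken code out of the trial, and it makes no provision for their day-7 efficacy data. This creates a risk of arm-dependent missing primary outcomes in both non-inferiority comparisons.

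The likely size is modest. With up to four exits in one compared arm and none in the other, the central shifts are under 2 points and the extremes just under 4. These figures rest on the assumed exit counts, on the assumed success among exits, and on applying 77.14% to both arms. The direction cannot be known from the article. The change is worth making because it costs little and because outcomes that were never collected cannot be restored at analysis.

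**What to change.** - In Exit criteria item (iv), Blinding and Safety assessments, state that the patient stops study drug but keeps the planned day-7 symptom scales, urine leukocytes and culture, and the 28-day visit if cured, unless consent is withdrawn.
- In Blinding, delete the automatic step from code break to trial withdrawal. Record who learned the allocation and when.
- Flag day-7 self-ratings given with the allocation known, and examine their influence in a sensitivity analysis.

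The cost is a wording change plus case report form fields for drug stop versus study exit and for who was unblinded. The visits are already planned and no further dosing is involved. The downsides are a few visits to chase after drug stop and a few self-ratings that may be given with the allocation known.

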## Randomization and allocation concealment

Randomization will be used for patient allocation [31]. The randomization will be performed by an independent statistician. The random numbers are divided into three groups sequentially: experimental group; control group 1; and control group 2. SAS 9.1.3 statistical software PROC PLAN procedure statements will be used, the seed number given, and randomized grouping tables will be generated for the 252 patients receiving treatment. On-site drug blinding will be carried out, and emergency unblinding procedures will be created. Blinded materials will be kept by a full-time investigator who will not participate in any part of the trial. During the trial, the investigator will be able to obtain the randomized number and drug number of each patient from the designated central randomized platform.

### Interventions

All researchers are clinical doctors and receive standardized training for the diagnostic interview before the start of the trial. LT are licensed for UTI with proven curative effect and safety [32]. Therefore, levofloxacin had been selected as the active control medicine. Participants in the experimental group will receive SJT plus LT placebo orally four times a day for seven days. Participants in control group 1 will take LT plus SJT placebo four times a day for seven days. Participants in control group 2 will take SJT and LT four times a day for the first five days and SJT plus LT placebo four times a day for the last two days. Patient visits are required after seven days of treatment. This is a placebo-controlled study; all participants receive the same number of pills with varying proportions of active drug and placebo to ensure that patients and clinicians are not aware of the allocated treatment aim. The SJT placebo is composed of 55% microcrystalline cellulose, 41% starch, 2% caramel, 1.5% silicon dioxide, and 0.5% talcum powder. The LT placebo is made of 56% microcrystalline cellulose, 42% starch, 1.5% silicon dioxide, and 0.5% talcum powder. The SJT and LT placebos are similar to the SJT and LT in size, color, shape, taste, smell, and packaging. SJT and its placebo and the LT placebo are produced by Guilin Sanjin Pharmaceutical Co., Ltd. and can be preserved for two years. LT is provided by First Sankyo Pharmaceutical (Beijing) Co., Ltd. at a dosage of 100 mg and can be preserved for two years. The recommended dosage of LT is 2–3 times a day, one pill at a time; hence, in order to meet the requirements of the blinding, the administration method of this medicine has been designed as described in Table 1.

**Table 1 Tab1:** Administration methods in the experimental and control groups

Time	Experimental group	Control group 1	Control group 2	
			First 5 days	Last 2 days
08:00	3 pills of SJT, 1 pill of LT placebo	3 pills of SJT placebo, 1 pill of LT	3 pills of SJT, 1 pill of LT	3 pills of SJT, 1 pill of LT placebo
12:00	3 pills of SJT	3 pills of SJT placebo	3 pills of SJT	3 pills of SJT
17:00	3 pills of SJT, 1 pill of LT placebo	3 pills of SJT placebo, 1 pill of LT	3 pills of SJT, 1 pill of LT	3 pills of SJT, 1 pill of LT placebo
22:00	3 pills of SJT	3 pills of SJT placebo	3 pills of SJT	3 pills of SJT

## Follow-up

All included patients will be re-evaluated after seven days of treatment follow-ups as an outpatient to assess the efficacy and safety. The patients who were cured will receive the second follow-up after 28 days to assess the recurrence rate. Patients whose symptoms worsened will receive a supply of relevant medicine and a written withdrawal schedule. Assessment of study endpoints and duration of follow-up is shown in Fig. 2.

**Fig. 2 Fig2:**
[figure not shown]
Standard Protocol Items: Recommendation for Interventional Trials (SPIRIT) figure

## Outcome measures

### Effective rate

The effective rate will be evaluated from three dimensions: symptoms; urine leukocytes; and bacteriological examination.

#### Primary outcome measure

The symptoms of acute uncomplicated lower UTI will be assessed. The assessment tools for symptoms of acute uncomplicated lower UTI are three participant self-rating scales (see Additional file 2): criteria sheet for evaluating the severity of urinary system infection (CSESUSI; mild: total score ≤ 8, moderate: total score 9–15, severe: total score ≥ 16), if the severity of the disease decreases from severe to moderate, or from moderate to mild, the symptoms are improved; symptoms score sheet of TCM (SSST; cure: total score = 0, effective: total score 0–6, invalid: total score ≥ 6); overactive bladder symptom score (OABSS; if the urgent urination score > 2 and total score > 3, OAB will be diagnosed; mild: total score ≤ 5, moderate: total score 6–11, severe: total score ≥ 12). The CSESUSI will use a scoring method to record the changes of symptoms and signs before and after treatment, such as shivering, fever, dysuria, urinal pain, urinary urgency, urinary frequency, lower abdomen distending pain, lumbago, and percussion tenderness over kidney region. The SSST uses a scoring method to record the changes of symptoms, tongue, and pulse in TCM before and after treatment. The OABSS has been found to be reliable and valid and highly responsive to treatment-related fluctuations in overactive bladder symptoms. Repeating the test after an acceptable treatment interval is an effective way to assess the efficacy of a particular drug regimen on OAB symptoms [33, 34]. If the symptoms disappeared after seven days of treatment, it indicates that the patient is cured. If these symptoms partially disappeared after seven days of treatment, it indicates that the treatment is effective but not cured. If there was no obvious remission and the symptoms of infection persisted after seven days of treatment, it indicates that the treatment is invalid.

#### Secondary outcome measure

(i)The urine leukocytes of 252 participants will be assessed. If the value of urine leukocytes is returned to normal after seven days of treatment, it indicates the patient is cured. If the value of urine leukocytes is reduced but not returned to normal after seven days of treatment, it indicates that the treatment is effective. If the value of urine leukocytes is still higher than the normal value after seven days, it indicates the treatment is invalid.(ii)The bacteriological examination of 252 participants will be assessed. If the original infected part of the specimen did not regenerate the original infected pathogen after seven days of treatment, it indicates the original bacteria is cleared. If the original pathogen was still cultured in the culture of the specimen from the original infection position, it indicates the original bacteria is not cleared.

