### Sample size

The effective rate will be taken as the main outcome measure of the clinical trial. According to a previous study, it showed that the effective rate of SJT was 77.14% in the treatment of simple bacterial lower urinary tract infection [25]. On the basis of a 0.9 power to detect a significant difference (α = 0.01, two-sided), 76 participants will be required for each group. 228 participants will be required for the three groups in a 1:1:1 ratio. Considering a 20% drop-out rate, we plan to include 252 patients in the whole trial.

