#### Criteria of comprehensive efficacy

(i)Criteria of cure: the evaluation of clinical symptoms reached the level of cure after seven days of treatment; the value of urine leukocytes returned to the normal value; the original infected bacteria was cleared after seven days of treatment. All three criteria must be met.(ii)Criteria of effective treatment: the clinical symptoms were alleviated but did not reach the level of cure after seven days of treatment; the value of urine leukocytes was reduced but not returned to normal after seven days of treatment. Either of these criteria must be met.(iii)Criteria of invalid treatment: the clinical symptoms were not alleviated after seven days of treatment; the value of urine leukocytes was still higher than normal after seven days of treatment; the original infected bacteria were still cultured from the original infection position after seven days of treatment. All three criteria must be met.

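### The cure, effective and invalid categories conflict on urine leukocytes and on the SSST, and the composite leaves 6 of its 18 outcome states without a category

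*Protocol article*

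**What the plan says.** Under Sample size, the protocol article states: "The effective rate will be taken as the main outcome measure of the clinical trial". The Effective rate section assesses that rate on symptoms, urine leukocytes and bacteriology.

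- **Symptoms (Primary outcome measure, under Effective rate).** Three self-rated scales are used. For the TCM symptom sheet: "SSST; cure: total score = 0, effective: total score 0–6, invalid: total score ≥ 6". For the CSESUSI: "if the severity of the disease decreases from severe to moderate, or from moderate to mild, the symptoms are improved". For the OABSS there are severity bands only: "mild: total score ≤ 5, moderate: total score 6–11, severe: total score ≥ 12". The paragraph closes with a verbal rule. Symptoms gone at day 7 means cured, symptoms partly gone means effective, and no clear remission with symptoms still present means invalid.
- **Leukocytes (Secondary outcome measure).** A normal value means cured and a lower but still abnormal value means effective. The last sentence reads: "If the value of urine leukocytes is still higher than the normal value after seven days, it indicates the treatment is invalid".
- **Composite (Criteria of comprehensive efficacy).** Cure needs symptom cure, normal leukocytes and clearance of the pathogen together. Effective needs symptoms relieved short of cure, or the leukocyte condition: "the value of urine leukocytes was reduced but not returned to normal after seven days of treatment. Either of these criteria must be met". Invalid needs unrelieved symptoms, leukocytes above normal and a persisting pathogen together.

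The article gives no order of precedence for a patient who meets two rules. It does not say which categories make up the effective rate.

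**The concern.** Response categories have to be exclusive and exhaustive before a rate can be computed from them. Here one patient can satisfy two opposite categories, or none, depending on the measure. The analyst must then choose which sentence to apply, and nothing in the article fixes that choice before the data are seen.

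The stakes are higher because Objective and design frames both principal aims as non-inferiority comparisons with levofloxacin. If the SSST bands were used in place of the verbal rule, unchanged low-scoring patients would count as effective. Each arm's rate would rise by its own share of such patients. If the less effective arm had the larger share, the difference between arms would shrink, which favours a non-inferiority claim.

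**Working it through.** The article states no figure to reproduce. The check applies the printed rules literally to every possible outcome.

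**1. Leukocytes** (Secondary outcome measure)

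| Day-7 state | Printed category |
|---|---|
| Normal | cure |
| Lower than baseline, still abnormal | effective and invalid |
| Not lower, still abnormal | invalid |

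The overlap covers the whole effective class. There is no gap.

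**2. SSST** (Primary outcome measure)

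| Score | Printed category |
|---|---|
| 0 | cure and effective |
| 1–5 | effective |
| 6 | effective and invalid |
| 7 or more | invalid |

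There is no gap here either. The bands use the day-7 total only, and the Inclusion criteria set no minimum entry score. A patient who enters at 5 and stays at 5 is effective by the band. By the verbal rule the same patient has had no remission and is invalid.

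**3. CSESUSI** (Primary outcome measure)

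The improvement clause lists falls from severe and from moderate. A patient who is mild at entry (score 8 or less) has no lower band to fall to, so none of the three transitions from mild can count as improved, even if the score reaches 0.

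**4. Composite** (Criteria of comprehensive efficacy)

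There are 3 symptom states × 3 leukocyte states × 2 culture results = 18 combinations.

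| Symptoms | Leukocytes | Pathogen cleared | Pathogen persists |
|---|---|---|---|
| Cured | normal | cure | none |
| Cured | reduced, abnormal | effective | effective |
| Cured | not reduced | none | none |
| Relieved | normal | effective | effective |
| Relieved | reduced, abnormal | effective | effective |
| Relieved | not reduced | effective | effective |
| Not relieved | normal | none | none |
| Not relieved | reduced, abnormal | effective | effective and invalid |
| Not relieved | not reduced | none | invalid |

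Totals: 1 cure + 9 effective only + 1 invalid only + 1 both + 6 none = 18. Of the 6 with no category, 3 have the pathogen persisting and 3 have it cleared. One example is symptoms gone, leukocytes normal and the pathogen still cultured.

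**5. Size on leukocytes**

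The planned arm is 252 / 3 = 84 patients. Let s be the share whose leukocytes are reduced but abnormal. The leukocyte effective rate changes by s, depending on which of the two sentences is applied. The documents do not give s, so the range below is assumed.

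| Assumed s | Patients of 84 | Change in rate |
|---|---|---|
| 5% | 4.2 | 5 points |
| 10% | 8.4 | 10 points |
| 20% | 16.8 | 20 points |
| 30% | 25.2 | 30 points |

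**The case against.** The best defence is that the primary measure already has a usable rule. The verbal symptom rule is ordered, essentially exclusive and tied to change from baseline. Under it, an unchanged patient is invalid, and a patient mild on the CSESUSI at entry whose symptoms disappear is cured. The clearest contradiction, on leukocytes, is in a secondary outcome, and the composite is not labelled primary. An SSST score of 0 does no harm if the effective rate pools cure and effective. The authors may have meant SSST above 0 and below 6, and leukocyte failure as no reduction. Additional file 2, which is not shown, may say how the scales are scored and combined. The move from severe to mild on the CSESUSI passes through both listed steps, so its absence is no real ambiguity.

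Much of this stands, and it limits the point. It does not remove it. The SSST bands still contradict the verbal rule printed in the same paragraph, and the shown text does not say which prevails or how the three scales feed that rule. A scoring sheet would not undo the leukocyte sentences or fill the composite gaps.

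Three stronger readings are tempting, and the documents do not support them:

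- **The rules inflate the effective rate in every arm.** This holds only if the SSST bands replace the verbal rule, and no share of unchanged low scorers is given.
- **Patients whose pathogen persists drop out of the composite.** Of the 9 such states, 3 are unclassified, 4 are effective, 1 is invalid and 1 is both.
- **Each scale is a separate primary test, with an inflated error rate.** The article presents the scales as tools for assessing symptoms and does not say that each is tested.

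**Conclusion.** The point holds as a contradiction in printed definitions. On leukocytes, the entire effective class is also invalid. On the primary symptom measure, the fault is narrower: score 6, unchanged patients scoring 1 to 5, a CSESUSI clause that cannot register improvement from mild, and no shown link from the three scales to the verbal rule. In the composite, 6 + 1 = 7 of 18 states do not fall in exactly one category.

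The 18 states are combinations, not patients, so 7 of 18 is not a proportion of the trial population. The 5 to 30 point range rests on assumed shares and applies to the secondary leukocyte rate. A reader might infer that overlaps and gaps affect every measure. They do not: leukocytes and the SSST only overlap, and the unassigned states are in the composite. Nor is the primary effective rate impossible to compute, because the verbal rule could carry it once the article says that it governs and how it is measured.

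**What to change.** Before unblinding:

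1. Make the verbal symptom rule the governing primary definition and state which scale puts it into numbers. Describe the other scales as supportive.
2. Align the SSST with it: cured = 0; effective = 1 to 5 and below baseline; invalid = 6 or more, or no reduction. This keeps the printed cut-off, so a patient who improves but still scores 6 or more is invalid. The text should say that this is intended.
3. Define leukocyte failure as above normal and not reduced from baseline.
4. Rewrite the composite so that each of the 18 combinations falls in exactly one category, with a stated precedence and a stated place for a persisting pathogen.
5. State that the effective rate is cure plus effective.

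The cost is rewording three paragraphs, with no new data collection. The sponsor should also check that the planning rate under Sample size ("it showed that the effective rate of SJT was 77.14% in the treatment of simple bacterial lower urinary tract infection") was measured on a definition comparable with the one chosen.

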**Methods/design:**

In this study, a randomized, double-blind, double-dummy, parallel control of positive drug, multicenter clinical study will be established. A total of 252 patients with acute uncomplicated lower UTI (syndrome of dampness-heat in the lower jiao) will be randomly allocated in the ratio of 1:1:1 to three groups: experimental group; control group 1; and control group 2. The experimental group receives Sanjin tablets plus levofloxacin tablets (LT) placebo; the control group 1 receives LT plus SJT placebo; and the control group 2 receives SJT plus LT on the first five days, SJT plus LT placebo on the last two days. Each group will be treated for seven days and followed-up 1–2 times. The primary outcome measures of effective rate and recurrence rate are symptoms. Secondary outcome measures of effective rate and recurrence rate are the urine leukocytes, bacteriology examination, and safety assessment. Outcomes will be assessed at baseline and after treatment.

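### Every patient whose urine leukocytes are reduced but still abnormal is both effective and invalid under the stated rules, so the secondary leukocyte effective rate has two values

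*Protocol article*

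**What the plan says.** The section Effective rate of the protocol article states: "The effective rate will be evaluated from three dimensions: symptoms; urine leukocytes; and bacteriological examination". The abstract gives leukocytes secondary status: "Secondary outcome measures of effective rate and recurrence rate are the urine leukocytes, bacteriology examination, and safety assessment".

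Item (i) under Secondary outcome measure then sets three day-7 grades:

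- Cured: "If the value of urine leukocytes is returned to normal after seven days of treatment, it indicates the patient is cured".
- Effective, for a value described as "reduced but not returned to normal after seven days of treatment, it indicates that the treatment is effective".
- Invalid: "If the value of urine leukocytes is still higher than the normal value after seven days, it indicates the treatment is invalid".

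Criteria of comprehensive efficacy uses the same two phrases again. Item (ii), the effective grade, is met by alleviated symptoms or by a leukocyte value that has fallen without normalising; one of the two is enough. Item (iii), the invalid grade, needs three things together, one of which is that "the value of urine leukocytes was still higher than normal after seven days of treatment".

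**The concern.** The effective rule compares the day-7 value with both baseline and the normal limit. The invalid rule looks only at the normal limit. A patient who improves without normalising satisfies both. This is not a borderline overlap at a cut-off: the whole effective grade lies inside the invalid grade, however large a fall is required to count as reduced.

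The numerator of the leukocyte effective rate then depends on which sentence the person classifying patients applies. The arms receive different active drugs, so the split between normalised and merely reduced may differ between them, and the two readings could order the arms differently. If the reading were settled after unblinding, the result could be settled with it.

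**Working it through.** The article states no figure for this outcome, so there is none to reproduce. The check is logical, followed by an illustration.

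**1. The rules written out.** Let B be the baseline value, P the day-7 value and U the upper limit of normal, with B > U.

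| Grade | Condition as written |
|---|---|
| Cured | P ≤ U |
| Effective | P < B and P > U |
| Invalid | P > U |

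The effective condition contains P > U, which is the whole of the invalid condition. Effective is therefore a subset of invalid, for any U and any minimum fall.

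**2. Literal application to a grid.** Inputs, all assumed: U = 5 (arbitrary), B from 6 to 60, P from 0 to 80, which gives 55 × 81 = 4,455 points.

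| Grades met | Points |
|---|---|
| Cured only | 330 |
| Invalid only | 2,640 |
| Effective and invalid | 1,485 |
| Effective only | 0 |

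All 1,485 points that meet effective also meet invalid.

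**3. Effect on the rate.** With C cured, E reduced but abnormal, and N patients in an arm:

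- if effective takes precedence, rate = (C + E)/N;
- if invalid takes precedence, rate = C/N;
- gap = E/N, which is zero only if E = 0.

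N = 252/3 = 84 per arm, from the planned total and the 1:1:1 allocation. C and E are not in the article. Assuming C = 42:

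| E (assumed) | (C + E)/N | C/N | Gap in points |
|---|---|---|---|
| 8 | 50/84 = 59.5% | 50.0% | 9.5 |
| 17 | 59/84 = 70.2% | 50.0% | 20.2 |
| 25 | 67/84 = 79.8% | 50.0% | 29.8 |

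**4. Comparison between arms.** For arms a and b, let c be the cured share and e the reduced-but-abnormal share. The difference in rates is (c_a − c_b) on the strict reading and (c_a − c_b) + (e_a − e_b) on the lenient one. The order reverses if arm a normalises fewer patients and e_a − e_b exceeds c_b − c_a. Nothing in the article says whether this will happen.

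**5. Comprehensive criteria.** Three symptom states (cured, alleviated, not alleviated), three leukocyte states (normal, reduced but above normal, not reduced and above normal) and two bacterial states (cleared, not cleared) give 3 × 3 × 2 = 18 combinations. Exactly one meets both item (ii) and item (iii): symptoms not alleviated, leukocytes reduced but above normal, pathogen still cultured.

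**6. Contrast with symptoms.** Under Primary outcome measure, the closing rule for symptoms makes treatment invalid only when symptoms persist and there has also been no clear improvement. That second condition separates invalid from effective. The leukocyte rule has no counterpart to it.

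**The case against.** The best answer is that the meaning is evident. Three ordered grades are listed, and if invalid took every value above normal, the effective sentence would govern nobody. The only reading that gives each sentence work to do makes invalid the remainder: above normal and not reduced. The symptom rule supports this. It is very probably what was intended, and it is the correction proposed here. But the text does not say it, gives no order of precedence, and repeats the unqualified phrase in the comprehensive criteria. Someone grading patients by the printed rule could count improved patients as failures.

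Other points stand as limits on the finding:

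- The percentages are assumptions, and the gap simply equals the assumed share. The conclusion rests on the set logic.
- All arms would be graded by the same rule, so the ambiguity does not by itself favour an arm. A change in the order of the arms is possible but has not been shown.
- A reduced leukocyte value alone cannot make a patient a comprehensive failure. Symptoms must also be unrelieved and the pathogen still present.
- The correction leaves any fall, however small, counted as effective. It also does not make the comprehensive criteria complete: six of the 18 combinations meet none of the three grades, for example symptoms cured, leukocytes normal and pathogen still cultured.

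**Conclusion.** The point holds. As written, leukocyte effective is wholly contained in leukocyte invalid, and the effective rate for this secondary outcome is either (C + E)/N or C/N. The containment assumes only that patients start above normal and that not normal means above normal. The size of the gap is E/N, which cannot be fixed from the article: 10 to 40 points per arm if 10% to 40% of patients are reduced but abnormal. In the comprehensive criteria the double grading is confined to one of 18 combinations. The symptom-based primary outcome and the sample size calculation do not use leukocytes and are unaffected. This is an error in a stated definition, not a detail left to an analysis plan. It should be corrected, but it does not threaten the main comparison.

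**What to change.** In item (i) of Secondary outcome measure, define leukocyte invalid as a day-7 value above normal and not reduced from baseline. Use the same words in item (iii) of Criteria of comprehensive efficacy. The three leukocyte grades are then normal; above normal but reduced; above normal and not reduced. They are disjoint and complete, and the effective rate has the single value (C + E)/N.

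The double-graded comprehensive combination disappears too. It becomes effective only, because item (ii) accepts a leukocyte reduction alone, so the trial team should confirm that this is what they want for a patient with unrelieved symptoms and a persisting pathogen. If a minimum fall is meant to count as reduced, state it in the same sentence, with falls below it graded as not reduced.

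The cost is one sentence in two places, dated before unblinding. Urine testing before enrolment and at the end of the trial is already planned, so no data are added.
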